### Randomization and blinding

The study randomization procedure will be done by a third person who will not be involved in this study. Each patient will receive a randomization code (determined through a computer-generated schedule). The random permuted blocks (15 blocks of 6) will be used to develop the randomization table. Vitamin D3 or placebo containers will be encoded based on the random codes. The odd and even numbers will be randomly allocated to groups A or B. The containers of vitamin D3 and placebo will be matched in appearance. As the containers will only be labeled with the codes without any further information, the patients will be blind in terms of intervention. The codes related to each group will be opened at the end of the study. In the present study both participants, the researchers and also statistical counselor will be blind in terms of the intervention.

### Withdrawal of participants

Participants who may withdraw prior to the randomization (during baseline phases I and II), will be replaced with new eligible participants. The exclusion criteria in this study would be as: have any acute illness, use less than 90% of the prescript supplement, would like to leave the study for personal reasons, participate in another study, immigrate and not available for following-up.

### Recruitment process

The study subjects will be selected from men referred to the infertility clinic of Ahvaz Jahad daneshgahi. After reading and reviewing the medical records of men referred to the center, the men with the primary inclusion criteria will be contacted by phone for an initial screening. The individuals interested in participating in the study will be invited for an in-person visit for further assessments.

### Procedures

The study flow diagram is given in Fig. 1. See additional file 1 for the Standard Protocol Items: Recommendations for Interventional Trials (SPIRIT) checklist. Questionnaires, measurements, and procedures as outlined in Fig. 2 (the SPIRIT diagram). The “Infertility Clinic of Ahvaz Jahad Daneshgahi Laboratory” will perform all laboratory analysis including analysis of blood and semen samples. The study visiting procedures are described in the following subsections.

**Fig. 2 Fig2:**
[figure not shown]
The schedule for enrollment, intervention and assessment based on the Standard Protocol Items; Recommendations for Interventional Trials (SPIRIT) Figure

### Baseline Phase I (Enrolment Phase): − 2 week

During visit 1, the final eligibility will be determined and a written consent will be obtained from participants by trained study staff. The information such as the procedures of the study, risks, side effects, confidentiality, voluntary participation, and right to withdraw will be provided to all participants. After consent is obtained, the study staff screens for drug abuse, obtains medical and concomitant medication histories, with eligibility determination based on the inclusion/exclusion criteria listed in Table 1. The necessary training to complete 3-day, 24-h recall questionnaires (including two week days and one weekend day) are given by a nutritionist to the participants and are asked to deliver them to the researcher during the second visit. In addition, participants are asked 2 to 7 days sexual abstinence to take semen samples. Semen and blood samples will be taken at the second visit.

### Baseline Phase II (Allocation Phase): 2 weeks (− 1, 0 weeks)

Once a participant is determined eligible, further demographic data, dietary intake, physical activity, sun exposure, anthropometric indices will be assessed, and blood and semen samples will be obtained during visit 2.

Demographic characteristics of patients are included: age (y), marriage duration (y), infertility duration (y), education, race, physical activity, sun exposure, time of sun exposure, sun exposure area, and sun screen use. The dietary intake will be evaluated using a 3-day, 24-h recall questionnaires (including two week days and one weekend day). Total energy, macronutrient, and micronutrient intake will be estimated using nutritionist IV software. The short form of the international physical activity questionnaire (IPAQ) will be used to evaluate physical activity levels [53]. The sun exposure time will be assessed with a questionnaire [54]. Anthropometric indices will be measured after overnight fasting, with minimal clothing and without shoes. Body weight and body fat percent will be measured with light clothes, no shoes and accuracy of 0.1-kg by Omron scale (Germany). Height will be measured without shoes with the accuracy of 0.5-cm by a stadiometer. Waist and hip circumferences will be measured by measuring meters (Seca, Germany). BMI will be computed by dividing the weight (kg) by the height squared (m^2^).

### Semen and blood samples

Semen samples will be obtained after 3 days of sexual abstinence. All semen samples will be held at 37C until the liquefaction. The sperm quality parameters such as ejaculate volume, total sperm count, sperm concentration, motility grade and sperm with normal morphology (%) will be assessed according to the WHO criteria [55]. The other biochemical analysis such as seminal levels of oxidative stress markers including malondialdehyde (MDA), 8-hydroxy-2- Dioxy Guanosine (8-OHDG) and total antioxidant capacity (TAC) and calcium will also be analyzed. Sperm DNA fragmentation will be assessed using sperm chromatin dispersion (SCD) method [11, 12].

Moreover, 10 cc of intravenous blood samples will be collected from patients to analyze biochemical parameters including 25 hydroxyvitamin D (25-OHD), oxidative stress index (TAC and MDA) and 8-OHDG, Sex hormones (total testosterone, estradiol (E2), luteinizing hormone (LH), follicle-stimulating hormone (FSH), sex hormone-binding globulin (SHBG), prolactin), parathyroid hormone (PTH), osteocalcin, calcium, and phosphorus.

The measurement of serum calcium and phosphorus and seminal calcium will be done using calorimetric method. Seminal and serum levels of vitamin D, TAC, MDA, 8-OHDG, PTH, osteocalcin, Testosterone, E2, SHBG, luteinizing hormone (LH), follicle-stimulating hormone (FSH), and prolactin will be assessed by enzyme-linked immunosorbent assay (ELISA).

During Baseline Phase II, the participants will be excluded if they have:
Body mass index (BMI) > 30 kg/m^2^Normal semen samples analysis for sperm motility (the mobility of sperm > 40% and rapid progressive sperm motility> 32%)Sufficient serum levels of 25OHD levels (> 30 ng / ml)Intense physical activity (> 3000 met/cal/week)

In visit 3 patients will be randomly allocated to either group A, receiving 4000 IU/d [51, 52] vitamin D3, or group B, receiving a matched placebo for 12 weeks (Randomization and blinding method described above).

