## Methods/design

### Study subjects

This trial will be conducted on 86 infertile men with idiopathic asthenozoospermia (the mobility of sperm < 40% and rapid progressive sperm motility < 32% [50], and with serum vitamin D levels < 30 ng / ml, who report inability to have a child after at least 1 y of marriage without using any preventive methods and with normal fertile female partner in the Infertility Clinic of Ahvaz Jahad daneshgahi, Iran. The further inclusion criteria are listed in Table 1.

**Table 1 Tab1:** Inclusion and exclusion criteria

Inclusion	
•Men aged 20 to 50 years	
•Idiopathic asthenozoospermia (the mobility of sperm < 40% and rapid progressive sperm motility < 32%	
•Serum vitamin D levels < 30 ng / ml	
•Access to the infertility clinic of Ahvaz Jahad daneshgahi, Iran	
•Inability to have a child after at least 1 y of marriage without using any preventive methods	
•Normal fertile female partner	
•No history (≤ 12 weeks) of medical therapy	
•Not having a history of epididymo-orchitis, prostatitis, genital trauma, testicular torsion, inguinal or genital surgery, urinary tract infection, or previous hormonal therapy, another genital disease (cryptorchidism, current genital inflammation or varicocele), a recent history of sexually transmitted infection, hepatobiliary disease and renal insufficiency, severe general or central nervous system disease and endocrinopathy, using cytotoxic medications, immunosuppressant, anticonvulsants, androgens, antiandrogens	
•No smoking, drug or alcohol abuse, and	
•No occupational and environmental exposure to possible reproductive toxins	
•Body mass index of < 30 kg/m^2^	
Exclusion	
• Have any acute illness	
• Use less than 90% of the prescript supplement	
• Would like to leave the study personally	
• Participate in another study	
• Immigrate	
• Not available for following-up	

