### Sample size

The sample size was calculated based on the progressive sperm ratio as the primary variable [29]. Considering a type I error of 0.05 and 90% for the power study, 34 patients were determined for each group. Also, regarding with the attrition rate of 25%, 43 patients will be included for each group. The formula used for the sample size was as follow:
$$ n=\frac{{\left({z}_1-\frac{\alpha }{2}+{z}_1-\beta \right)}^2\left({\delta_1}^2+{\delta_2}^2\right)}{{\left({\mu}_1-{\mu}_2\right)}^2} $$

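### The visit-2 semen exclusion is not the complement of the inclusion definition, so a man whose trial sample is normal on only one motility criterion can be randomised

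*Protocol article*

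**What the plan says.** The Protocol article gives two motility rules with the same cut-offs. Both quotations below stop just before the final percent sign.

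- **Inclusion** (Study subjects; repeated in the Abstract and Table 1): "idiopathic asthenozoospermia (the mobility of sperm < 40% and rapid progressive sperm motility < 32". Both values must be low.
- **Exclusion during Baseline Phase II** (Semen and blood samples): "Normal semen samples analysis for sperm motility (the mobility of sperm > 40% and rapid progressive sperm motility> 32". Both values must be high.

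The order of events is also stated:

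- **Before visit 1** (Recruitment process): men are picked out by reviewing clinic records and then screened by phone.
- **Visit 1** (Baseline Phase I): "During visit 1, the final eligibility will be determined and a written consent will be obtained from participants by trained study staff". The criteria applied are those of Table 1.
- **Visit 2**: the same section adds "Semen and blood samples will be taken at the second visit". Baseline Phase II keeps this order: "Once a participant is determined eligible, further demographic data, dietary intake, physical activity, sun exposure, anthropometric indices will be assessed", with blood and semen sampling at that visit.
- **Visit 3** (end of Semen and blood samples): "In visit 3 patients will be randomly allocated to either group A". No semen check is described between the Phase II exclusions and this step.

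**The concern.** Each rule reads naturally alone, but they do not divide men into eligible and ineligible. A man who is normal on exactly one measure fails the definition and also escapes the exclusion. The Phase II list is the only rule that the text ties to the trial's own semen sample, so nothing stated there stops him from being allocated.

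The combination is not far-fetched. Rapid progressive sperm are a subset of motile sperm, so total motility above 40% with rapid progressive motility below 32% is coherent. Men chosen because an earlier recorded value was low will also tend to drift upward on a repeat sample, and some may cross one cut-off and not the other.

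The title, the objective and the listed outcomes all refer to asthenospermic men, and the Practical aims section would turn a favourable result into a recommendation for them. Two staff members following the same text could also decide differently on the same man.

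**Working it through.** No figure in the plan has to be reproduced; this is a check of logic. Write T for total motility (%) and R for rapid progressive motility (%), with R no greater than T.

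**Step 1. The rules.**
- Include (Study subjects, Table 1): T < 40 and R < 32.
- Exclude at visit 2 (Semen and blood samples): T > 40 and R > 32.

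**Step 2. The complement.** The negation of (T < 40 and R < 32) is (T ≥ 40 or R ≥ 32). The written exclusion differs in its connective (*and* instead of *or*) and in its inequality (> instead of ≥).

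**Step 3. The worked case.** Take T = 55, R = 20.
- Inclusion: 55 < 40 is false, so the sample does not meet the definition.
- Exclusion: 55 > 40 is true but 20 > 32 is false, so he is not excluded.

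**Step 4. All combinations.** Whole-number pairs from 0 to 100 with R ≤ T number 101 × 102 / 2 = 5,151.

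| Status of the pair | Pairs |
|---|---|
| Meets inclusion | 784 |
| Fails inclusion, excluded at visit 2 | 2,310 |
| Fails inclusion, not excluded at visit 2 | 2,057 |

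The last row splits into:
- T > 40 and R < 32: 60 values of T × 32 values of R = 1,920.
- T < 40 and R > 32: 1 + 2 + … + 7 = 28, few because R cannot exceed T.
- T = 40 or R = 32: 41 + 69 − 1 = 109.

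These counts show which combinations the wording lets through. They say nothing about how many patients fall there.

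**Step 5. The complement put in place.** With the visit-2 exclusion written as T ≥ 40 or R ≥ 32, the third row becomes 0: every pair either meets inclusion or is excluded.

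**Step 6. Does another step close the gap?** The Table 1 decision is placed at visit 1, semen is taken at visit 2 and allocation is at visit 3. No section says that the Table 1 motility criterion is applied again to the visit-2 result.

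**The case against.** **Table 1 may still apply at visit 2.** Nothing says that the Phase II list replaces Table 1, and inclusion and exclusion rules normally operate together. Table 1 also sets limits for 25-OHD and BMI, which the trial measures at visit 2, so applying Table 1 to visit-2 results is a plausible reading. This stands in part. A reader might infer that discordant men *are* randomised; the text supports only that they *can be*.

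**The visit-2 sample may be a deliberate second look.** A man reaching visit 2 has already been judged to qualify, and requiring a fully normal repeat sample before removing him is a defensible design. That is fair, but the article does not say this is the intent. If it is, the population description should say that the definition rests on the earlier recorded value.

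**Loss of power.** A reader might infer that these men dilute the effect. The documents cannot support a figure. The Sample size section says "Considering a type I error of 0.05 and 90% for the power study, 34 patients were determined for each group" but gives no means or SDs; 34 per group implies a standardised difference of about 0.79 only by working backwards. With power = Φ(0.786 × k × √17 − 1.96), k = 1 returns 90%. If 20% of men were discordant, power would be about 74% if they showed no effect (k = 0.8) and about 83% if they showed half the effect (k = 0.9). Both the share and the effect are invented inputs, so no loss is claimed.

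**Less room to improve.** This inference fails too. The sample size is based on the progressive sperm ratio, and the man with 55% total and 20% rapid progressive motility has as much room on rapid progressive motility as an included man with the same value.

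**Internal validity.** Any such man is present before allocation and can enter either arm, and the ANCOVA adjusts for baseline. This stands: the treatment comparison is not biased.

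**Details in the same lists.** Values exactly at a cut-off (40%, 32%, 30 ng/ml, BMI 30) and the intense-activity exclusion missing from Table 1 are editorial points.

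**Conclusion.** The point holds as an inconsistency between two explicit eligibility rules. It does not depend on anything the article may have left to a fuller document. As written, a man whose visit-2 sample is normal on one motility criterion only can reach randomisation although that sample does not meet the trial's definition of asthenozoospermia.

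Its size in patients is unknown. The conclusion assumes only that the stated visit order is followed and that Table 1 is not re-applied to the visit-2 sample, which the text neither requires nor rules out. The harm is to the population named in the conclusion and to consistent enrolment. The matter should be corrected because the remedy is cheap and motility both defines the population and drives the sample size.

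**What to change.** 1. Reconcile the inclusion definition (Study subjects, Table 1) with the Baseline Phase II exclusions, so that one stated rule governs the visit-2 semen sample. Which rule was intended is for the investigators to say. If it is the Table 1 definition, the visit-2 exclusion must be its exact complement, joined by *or* and covering the boundary values: T ≥ 40 or R ≥ 32.
2. Keep every randomised man in the intention-to-treat analysis, as the Statistical analysis section already defines it.
3. Add a sensitivity analysis restricted to men whose visit-2 sample meets both cut-offs, and report how many in each arm do not. The restriction uses a measurement taken before allocation, so it does not select on anything that follows treatment.

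**Cost.** A small text change, a few more screen failures, and one extra analysis from data already collected. Recruitment began in April 2018 and was expected to finish in September 2021, so a late change could leave men enrolled under two rules. The sensitivity analysis covers that, because it applies one definition to everyone whenever they were enrolled.

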### Treatment phase (12 weeks)

In this phase (visit 4), the patients will be asked to use vitamin D3 and placebo supplements one pill every day for 12 weeks. Also, the patients will be asked not to change their diet, not to participate in any other clinical trials, and not to take any medications or supplements without consulting the researchers during this time. The compliance of patients to use the supplements will be done through either contacting by phone or sending a phone message every day in this phase.

### Follow up phase (12 weeks after baseline)

In visit 5, all measurements such as anthropometric indices, physical activity, dietary intake, and sun exposure will be assessed and blood and semen samples will be collected.

### Compensation

All supplements and tests will be free of charge for participants in this study. Also, the transportation costs will be paid. In addition, at the end of the study, free nutritional counseling will be provided to all patients.

### Data management and monitoring

Participants’ information, all forms completed by them and their test results will be held confidential throughout all stages of the research cycle and biological samples will be stored in a protected area with limited access. Trial data will be checked in regard of accuracy and following standard operating procedures and policies during study, by an independent data management team at Ahvaz Jundishapur University of Medical Sciences.

### Statistical analysis

Intention-to-treat (ITT) and per-protocol (PP) populations will be used in the analysis. The ITT population consists of all individuals who will be randomized, whereas the PP population consists of all participants who complete the 12-week intervention. All data will be analyzed using SPSS (Version 22; SPSS Inc., Chicago, IL). Results will be expressed as mean ± SD and frequency and (percentage) for quantitative and qualitative variables respectively. The normal distribution of variables will be tested and confirmed by Kolmogorov-Smirnov test. The baseline differences of mean values between groups will be tested using independent sample t-test or Mann-Whitney U test for normal and non- normal distribution variables respectively. Analysis of covariance (ANCOVA) will be used to identify any differences between the two groups at the end of study, adjusting for baseline values and covariates (such as BMI, age, dietary intake including dietary calorie, calcium, F, selenium, vitamin C, E, A, D and zinc, physical activity, sun exposure, season, serum vitamin d, PTH and calcium). The comparison of mean values within groups pre- and post-intervention will be done by paired sample t tests and Wilcoxon signed-rank test as nonparametric alternatives for normal and non- normal distribution variables respectively. Differences will be considered statistically significant at *P* < 0.05.

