### Primary aim

The primary aim of the present study is to improve serum levels of 25OHD3 through vitamin D3 supplementation in order to evaluate its effects on fertility in infertile men. The compliance of subjects will be monitored by counting the remaining supplements. The subjects who may not use greater than 90% of the supplements will be excluded. We expect that the drop-out rates will be high in this study. Therefore, we would consider a 25% attrition rate for each group of study.

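### The ITT set is defined as all randomised men, but the exclusion rules and the single week-12 sample reduce it, as written, largely to the per-protocol set

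*Protocol article*

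**What the plan says.** The Statistical analysis section names two populations: "The ITT population consists of all individuals who will be randomized, whereas the PP population consists of all participants who complete the 12-week intervention". The between-group method is then fixed: "Analysis of covariance (ANCOVA) will be used to identify any differences between the two groups at the end of study, adjusting for baseline values", plus a list of covariates. The within-group method is also fixed: "The comparison of mean values within groups pre- and post-intervention will be done by paired sample t tests and Wilcoxon signed-rank test".

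The Primary and Secondary outcomes sections define every outcome as a pre/post change. After baseline, the text gives one occasion for blood and semen. The follow-up section says: "In visit 5, all measurements such as anthropometric indices, physical activity, dietary intake, and sun exposure will be assessed and blood and semen samples will" (the sentence closes with their collection). The schedule figure is not shown, so the single sampling point rests on the text.

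Table 1 and the Withdrawal of participants section list acute illness, use below 90% of the supplement, personal withdrawal, joining another study, emigration and unavailability for follow-up as reasons for exclusion. Apart from acute illness and another study, these can in practice arise only after randomisation. The Primary aim section repeats the 90% rule as grounds for exclusion. Men who withdraw before randomisation are replaced; nothing says that men excluded later are still sampled or analysed.

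On the scale of loss, the Primary aim section expects high drop-out and adds: "Therefore, we would consider a 25% attrition rate for each group of study".

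**The concern.** An ITT analysis is meant to estimate the effect in everyone randomised, and setting it beside a per-protocol analysis is meant to show how far drop-out and non-adherence matter. That works only if men who leave, stop or under-use the capsules can enter the first analysis and not the second. Here two stated rules work against it. The exclusion rules remove such men after randomisation, and the stated tests drop any man without a visit-5 value.

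The two results would then agree mainly because they rest on nearly the same men, yet the agreement would read as robustness. If leavers benefit less than stayers, the result labelled ITT would overstate the effect in all randomised men on 25-OHD and the sperm parameters. The Practical aims section makes a recommendation to supplement depend on the trial's findings.

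**Working it through.** **1. The plan's own figures.** The Sample size section gives 34 per group (type I error 0.05, power 90%) and 43 per group after a 25% allowance.
- 34 × 1.25 = 42.5, rounded up to 43, so 43 reproduces. (Dividing instead, 34 / 0.75 = 45.3, gives 46. That is a separate matter.)
- The 34 cannot be rebuilt, because the means and SDs are not given. Solving the printed formula, read as two-sided, for the standardised difference gives d = (1.960 + 1.282) × √(2/34) = 0.786.

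**2. Who can enter each stated analysis.**

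| Man | In ITT by definition | In per protocol by definition | Enters the stated tests |
|---|---|---|---|
| Completes, gives visit-5 sample | yes | yes | yes |
| Stops or under-uses, attends visit 5 | yes | no if he stopped; not addressed if he only under-used | only if the exclusion rule does not remove him |
| Leaves, no visit-5 sample | yes | no | no |

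The second row alone can separate the two results, and it is the row on which the exclusion rules bear.

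**3. The mechanism.** In one simulated data set of 86 men, 22 of them without an end value, ANCOVA on all 86 and ANCOVA on completers used the same 64 men and gave the same estimate, 0.7759.

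**4. How many men.** 25% of 86 is 21.5, which leaves 64.5. Suppose a share of those 21.5 still gives a visit-5 sample and is analysed (assumed range):

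| Share | ITT men with an outcome | Completers |
|---|---|---|
| 0% | 64.5 | 64.5 |
| 25% | 69.9 | 64.5 |
| 50% | 75.3 | 64.5 |
| 75% | 80.6 | 64.5 |
| 100% | 86 | 64.5 |

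**5. Size of the bias, adverse case.** Assume that none of the 25% is sampled, that active-arm leavers have no effect, and that stayers have the design effect of 0.786 SD.
- All-randomised effect: 0.75 × 0.786 = 0.590 SD. The completer analysis estimates 0.786 SD.
- Overstatement: 0.25 × 0.786 = 0.197 SD. At 10% loss it is 0.10 × 0.786 = 0.079 SD.
- Completers per arm: 43 × 0.75 = 32.25. Standard error = √(2/32.25) × √(1 − r²), where r is the correlation of baseline with week 12. This gives 0.249 (r = 0), 0.216 (r = 0.5) and 0.178 (r = 0.7), so the bias is 0.79, 0.91 or 1.11 standard errors.
- If loss is unrelated to outcome given baseline, the bias is zero.

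**6. Which remedy responds.** The adverse case was simulated with r = 0.5, 43 per arm, 1,500 trials and 20 imputations:

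| Analysis | Mean estimate (SD units) |
|---|---|
| All randomised, outcomes known | 0.59 |
| Completer ANCOVA | 0.79 |
| Multiple imputation by arm from baseline | 0.79 |
| Missing active-arm values imputed from placebo | 0.59 |

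Imputation by arm reproduces the completer result. Placebo-based imputation recovers the all-randomised effect here because its assumption is the one built into the scenario.

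**The case against.** The strongest objection is that this is only silence. The article defines ITT correctly and never says that the ITT analysis is complete-case. Handling of missing data is commonly left to an analysis plan or full protocol, neither of which is shown. That stands as far as an imputation rule goes: its absence is not an error, and an unseen document may hold one. It does not dispose of the conflict between stated rules, which is an all-randomised population in one section and exclusion after randomisation in three others, with no statement that excluded men are followed or analysed.

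A reader might infer that a quarter of the men will give no visit-5 sample. The documents do not say so. The 25% is an attrition allowance, stated directly after the 90%-use rule, and may include poor adherers who could attend. The Discussion does link it to withdrawal, so withdrawal is part of it, but the share is unknown.

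A reader might also infer that the two populations are the same men. That goes too far. Per protocol is defined by completing the intervention, not by having a sample. A man who stops the capsules but attends visit 5 belongs to ITT alone, unless the exclusion rule removes him.

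Finally, the 0.20 SD is simply 25% of 0.786 under an adverse assumption. That is correct, and it should be read as an upper illustration.

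**Conclusion.** The point holds in limited form. The ITT definition conflicts with the post-randomisation exclusions. With one post-baseline sample and tests that need it, the ITT result as written falls on men with a visit-5 value, largely the per-protocol set. Agreement between the two analyses would say little about robustness to drop-out.

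The effect on the estimate is conditional. It ranges from zero, if loss is unrelated to outcome given baseline, through 0.08 SD at 10% loss, to about 0.20 SD at 25% loss. The last two figures assume that active-arm leavers have no effect, that none of them is sampled, and that the true effect among stayers is the implied 0.786 SD. The documents support neither an expected overstatement of one third (0.197 / 0.590) nor the claim that both analyses must give the same estimate.

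The matter is worth correcting because the remedy is cheap and the Trial time-scale section places the trial still in enrolment.

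**What to change.** - Reconcile Table 1, Primary aim and Withdrawal of participants with the ITT definition. State that men who stop or under-use the capsules but remain willing are still asked for the visit-5 blood and semen samples and are analysed in their randomised group. Adherence would then define the per-protocol set and not removal from the trial's data. This concerns data collection only, not treatment.
- Add one sensitivity analysis for the primary outcomes in which missing week-12 values in the active arm are imputed from the placebo arm.
- Report the number missing and the reasons, by arm.
- Label any analysis limited to men with a visit-5 value as exactly that, not as ITT.

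Multiple imputation by arm from baseline variables is optional. It would let all 86 men be counted, but it gives essentially the completer answer and does not address the concern.

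The cost is a wording change, some effort to bring back willing men for a visit already scheduled, and slightly more analysis work. No extra patients, visits or types of assay are needed. The sensitivity estimate may be less favourable than the completer estimate.
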